## Abstract

**Background:**

Polycystic ovary syndrome (PCOS) affects up to 20% of women and is characterised by higher amounts of visceral fat, obesity, insulin resistance, dyslipidemia and reproductive and cardiometabolic complications. Increased oxidised low-density lipoprotein (LDL) concentrations have been associated with an increased risk of cardiovascular disease (CVD)-related events. Oxidised LDL is rarely used as a marker for CVD risk in PCOS-related studies despite its widely accepted role in atherogenesis and the increased risk factors associated with PCOS. Additionally, prolonged periods of sedentary behaviour can negatively affect metabolic health. No studies have specifically examined the effects of reducing sedentary behaviour on CVD risk in PCOS with a lifestyle physical activity intervention. The aim of the current study is to measure the feasibility of a randomised controlled trial (RCT) examining the effects of supervised exercise and reducing sedentary behaviour in women with PCOS on CVD risk.

**Methods/design:**

A feasibility, exploratory RCT will be conducted. Fifty-one pre-menopausal females will be randomly allocated between an exercise group (EG), a lifestyle physical activity group (LPAG) and a control group. Participants in the EG will undertake a 12-week supervised aerobic exercise programme. The LPAG will aim to increase daily physical activity and reduce sedentary behaviour for 12 weeks. The control group will not take part in any intervention. Primary outcomes are feasibility and acceptability of the intervention and procedures. Secondary outcomes are oxidised LDL, aerobic fitness, blood lipid profile, fasting glucose and insulin, testosterone and inflammatory markers.

**Discussion:**

PCOS is associated with various increased risk factors for CVD, including hypertension, dyslipidemia, abdominal obesity, insulin resistance, and inflammation. Whether oxidised LDL has a role in this increased risk is not yet known. The present study aims to measure the feasibility of implementing structured exercise training and/or increased lifestyle physical activity in women with PCOS, so that a subsequent adequately powered RCT can be designed. The results from the study will be used to refine the interventions and determine the acceptability of the study design. A limitation is that some self-monitoring in the lifestyle physical activity group may not be reliable or replicable, for example inputting information about time spent cleaning/gardening.

**Trial registration:**

ClinicalTrials.gov, NCT03678714. Registered 20 September 2018.

## Background

Polycystic ovary syndrome (PCOS) is the most common endocrine disorder of reproductive age, affecting 15–20% of women [1]. The diagnostic ‘Rotterdam’ criteria state that women must present with two of the following three signs/symptoms—hyperandrogenism, chronic anovulation/oligomenorrhea, and polycystic ovaries—in the absence of other diseases that promote these symptoms [2]. PCOS is characterised by higher amounts of visceral fat, obesity, and insulin resistance [3] and associated with reproductive and cardiometabolic complications [4].

Dyslipidemia is prevalent in up to 70% of women with PCOS [5]. The lipoprotein profile of women with PCOS is characterised by elevated plasma triglycerides (TG) and reduced high density lipoprotein (HDL) concentrations [6]. Women with PCOS are at increased risk of cardiovascular disease (CVD) compared with weight-matched counterparts. Given the large proportion of lean and overweight women who are affected by PCOS, it is prudent to examine how CVD risk can be mitigated in this high-risk population. Structured exercise has a positive impact on women with PCOS and programmes of 12 to 24 weeks can improve ovulation rates and insulin sensitivity, and aid weight loss [3].

To our knowledge, no studies have examined the impact of lifestyle physical activity and reducing sedentary behaviour on CVD risk in women with PCOS. In addition, oxidised low-density lipoprotein (LDL) is rarely used as a marker for CVD risk in PCOS-related studies despite its widely accepted role in atherogenesis. Increased oxidised LDL concentrations have been associated with an increased risk of CVD-related events and have been shown to accurately predict coronary artery disease [7–9]. Total cholesterol:high-density lipoprotein (TC:HDL) ratio and abdominal obesity are both positively correlated with oxidised LDL [7, 10]. Hence, considering the high prevalence of dyslipidemia and visceral fat in PCOS populations, they may have a higher risk for elevated oxidised LDL concentrations.

Additionally, research pertaining to the cardiometabolic profile in women with PCOS has often produced inconsistent results, possibly due to the wide range of PCOS phenotypes possible once classified by the Rotterdam criteria [11]. Phenotypes that present with hyperandrogenism have been shown to have a worse metabolic profile and increased cardiovascular risk factors than other phenotypes, despite comparable distributions of body weight [11]. Regardless, there are no specific guidelines for this higher risk phenotype.

Finally, recent research has emphasised that even when adults meet physical activity guidelines of 150 min/week [12], prolonged periods of sedentary activity still negatively affect metabolic and general health [13, 14]. High levels of sedentary behaviour promote hyperinsulinemia and subsequently affect insulin sensitivity and glucose concentrations [13], and as such sedentary behaviour may be an exacerbating factor of PCOS.

Before an adequately powered RCT measuring the effects of exercise and/or increased lifestyle physical activity on such indicators of cardiovascular health can be designed, the interventions must be refined and a sample size must be calculated.

Therefore, the specific aims of the present feasibility study are the following:
Assess the feasibility of conducting a randomised-controlled trial (RCT) of exercise training and increased physical activity in women with PCOSIdentify the use of partitioning participant data by androgen profileMeasure rates of recruitment and retentionMeasure rates of attendance and compliance with the supervised exercise programmeConduct post-intervention interviews with completers and dropouts to refine the interventions and assess barriers to physical activity, and how they can influence future exercise interventions in women with PCOSObtain a standard deviation for oxidised LDL so that a sample size for a future, larger-scale RCT can be calculated

## Methods/design

### Study design

This study is a feasibility study involving an exploratory RCT. Fifty-one adult females with PCOS who are aged 18 years or over and pre-menopausal will be randomly assigned to a 12-week exercise intervention, an increased lifestyle physical activity group, or a control group. Outcomes will be measured pre- and post- intervention. Interview sessions will be undertaken with a proportion of participants at the end of the trial to provide qualitative information regarding barriers and facilitators to increased physical activity. The study is being conducted at the Centre for Sport and Exercise Science (CSES), Sheffield Hallam University, Sheffield, UK. Sheffield Teaching Hospitals, Sheffield, UK, will be used as a participant recruitment centre.

The study duration is from September 2018 up to May 2021 and is sponsored by CSES, Sheffield Hallam University.

### Recruitment of participants

Participants will initially be screened according to inclusion criteria by a clinical member of the research team via a computerised search of their notes. Afterwards potential participants will be sent information packs about the research, including an invitation letter and participant information brochure. Email and contact information for the researcher will be included in the packs and potential participants will be given a minimum of 24 h and a maximum of 14 days to respond. It will be clearly stated in the invitation letter that there is no obligation or pressure to participate in the study and that if patients do not wish to participate, their future medical care will not be jeopardised.

Volunteers wishing to participate in the study will be requested to contact a member of the research team or respond via letter by a specified date. Participants who respond to the letter of invitation and satisfy triage through telephone pre-screening will be invited into CSES of the Sheffield Hallam University for their initial session, where they will provide written informed consent and have an opportunity to familiarise themselves with the protocol and ask questions. They will then undertake baseline assessments.

It will be assumed that those who haven’t contacted the research team could still potentially have an interest in study participation but may be too busy to respond. They will be re-contacted via telephone (or sent a follow-up letter if telephone contact cannot be established) to remind them of the invitation to the study. Potential participants who decline to volunteer or who do not respond to the follow-up letter will not be contacted further, since it will be assumed that they do not wish to participate in the study.

### Eligibility criteria

Participants eligible for the trial must meet the below inclusion criteria as follows:
i)Women diagnosed with PCOS according to the Rotterdam criteria 2003, National Institute of Health (NIH) 1990 criteria or Androgen Excess and Polycystic Ovary Syndrome (AE-PCOS) Society 2006 criteriaii)Have experienced menarche (their first menstrual bleeding) and be at least 18 years of ageiii)Are English speakingiv)Are physically able to perform exercise

Exclusion criteria include:
i)Post-menopausal statusii)Are smokersiii)Are undertaking regular structured exercise defined as > 150 min/weekiv)If taking metformin, have been taking it for < 3 monthsv)Are taking the oral contraceptive pill (OCP) or have taken it in the last monthvi)Have any medical condition that may be responsible for the symptoms of PCOS, such as congenital hyperplasia, androgen-secreting tumour, hyperprolactinemia, or Cushing’s syndromevii)Have current, clinically defined CVD or a history of cardiac events

Participants will be advised that commencement of any of the above-mentioned medications during the trial is a contraindication and they will be withdrawn from the trial.

### Baseline and post-intervention measurements

During visit 1, after written informed consent has been obtained and eligibility confirmed by AW, the following baseline tests measurements will be made: age, anthropometric measures (stature, body mass, hip and waist measurements), finger-prick and venous blood sampling (see Outcome measures for a detailed description of analytes), aerobic fitness assessed by the Astrand-Rhyming single stage test (see Outcome measures for detailed description).

After completion of the intervention, all tests and measurements will be repeated.

### Randomisation and masking

Participants will be randomised in equal numbers between a supervised exercise programme, a lifestyle physical activity group and a control group. This will be undertaken using a computerised randomisation programme (QuickCalcs, GraphPad Software, USA) by an experienced researcher who is not involved in the study assessments. Allocation will be placed in sequentially labelled opaque envelopes. Each envelope will be offered to the participants, in sequence, by the chief investigator, on completion of their baseline assessments. It is not possible to mask participants or research team to the allocated intervention. Outcome assessors will be blinded to group allocation for anthropometric and fitness measures, but blood assays will be carried out by the same member of the research team. This is because blood assays are not considered to be subjective and are unlikely to be affected by outcome assessor bias.

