#### Secondary outcomes

Serum oxidised LDL is the secondary outcome of the current study and will be analysed by enzyme-linked immunosorbent assay (ELISA). Optical density will be measured using an electronic plate reader and can be used to determine the quantity of the specific antigen in the blood using a calibration curve.

ELISA will also be used for quantitative analysis of C-reactive protein, neopterin, TBARS, fasting insulin and sex hormone binding globulin (SHBG). Free testosterone will be measured using a liquid chromatography method. This method has been chosen due to its ability to detect small amounts of serum testosterone, particularly in lower concentrations in females [20]. Free testosterone will be quantified using a calibration curve and calculating peak area.

Aerobic fitness will be assessed using the Astrand-Rhyming test. This is a submaximal single-stage test performed on a cycle ergometer, lasting between 6 and 7 min [21]. The goal is to obtain heart-rate values between 125 and 170 beats per minute (bpm) for a given work-rate at 50 revs/minute (50 or 75 watts for unconditioned women) [21]. Heart rate is then measured at the fifth and sixth minute if steady state (a difference ≤ 5 bpm is achieved), and the average of the two heart-rate measurements can be used to estimate VO_2max_ according to a nomogram. This value must be adjusted for age to account for decreasing maximal oxygen uptake and maximal heart rate with age [19].

For lipid profile (including LDL-cholesterol, HDL-cholesterol, TG and TC) and fasting glucose, a Cholestech Automated Analyser will be used. A fingerprick blood sample is obtained and collected into a capillary tube. The sample is then inserted into the machine cassette. This produces an automated reading from the sample in which accuracy can be maintained by using control samples and calibrations. HDL sub-fractions will be measured using gel electrophoresis.

In order to measure the amount of lifestyle physical activity (and subsequent sedentary activity), the long-form International Physical Activity Questionnaire (IPAQ) will be administered at baseline and post-intervention to all participants. This will be used to compare differences in time spent sitting, both during the week and weekend, and the amount of lifestyle physical activity (including transport, housework, and leisure time) undertaken.

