### Data collection, monitoring, management and storage

Data will be collected by the chief investigator (AW) using data collection forms and entered into a computerised database. Range checks will be carried out to ensure data quality. Data checks will frequently be completed by other members of the research team.

Participants’ names will be anonymised and replaced with a code using a computerised pseudonymisation programme (Open Pseudonymiser, University of Nottingham, UK). All other study data will be stored securely on Sheffield Hallam University premises and/or saved on encrypted computer drives on site. Only the research team will have access to the data, including the final trial dataset. Data will be securely archived after study closure and stored for up to 7 years, when it will be destroyed. All data will be stored and managed according to Sheffield Hallam University’s confidentiality and data protection policies.

Due to the low risk involved in this study, no formal data monitoring committee will be formed. However, the study will be regularly monitored by the research team members being led by a senior team member (MK) who will meet at regular intervals throughout the study period.

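### Blinded follow-up assessment is claimed but not squared with the chief investigator's roles, and the blood assays are left unblinded although coded samples would be easy

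*Protocol article*

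**What the plan says.** All statements are in the protocol article.

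- **Allocation (Randomisation and masking).** The sequence is generated "by an experienced researcher who is not involved in the study assessments". The envelopes are then handled by someone else: "Each envelope will be offered to the participants, in sequence, by the chief investigator, on completion of their baseline assessments".
- **Masking (same section).** "It is not possible to mask participants or research team to the allocated intervention". The next sentence says: "Outcome assessors will be blinded to group allocation for anthropometric and fitness measures". The blood assays are set apart from this and assigned to a research team member, on the ground that "blood assays are not considered to be subjective and are unlikely to be affected by outcome assessor bias".
- **Data collection (Data collection, monitoring, management and storage).** "Data will be collected by the chief investigator", on forms that are then entered into a database. The section also plans to replace names with a code from a pseudonymisation program.
- **Assays (Secondary outcomes; Blood sampling and storage).** Oxidised LDL is measured by ELISA and read off a calibration curve. For the androgen measure, "Free testosterone will be quantified using a calibration curve and calculating peak area". Serum is frozen until it is analysed, and the assays are done at the university by a research team member.

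**The concern.** The chief investigator learns every allocation by offering the envelopes, and is also the only person named as collecting data. The measures said to be blinded depend on the observer. Waist is taped at the narrowest point of the torso, which the assessor must find. The Astrand-Rhyming test depends on the choice of work-rate, on accepting steady state (two heart rates within 5 bpm) and on a nomogram. All of these are repeated after the intervention, when allocation is known to anyone who saw the envelopes. If the chief investigator does the repeat measurements, the trial would report blinded assessment that it did not have.

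The assay question is separate. The protocol does not claim blinding there; it argues that blinding is unnecessary. But fitting a calibration curve and integrating a chromatogram peak can involve choices by the analyst, and the analyst comes from a team described as unmaskable. Oxidised LDL is the lead biomarker, and free testosterone decides whether a woman is classed as normo- or hyper-androgenic.

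This matters even in a feasibility study. Suitability of the measurement procedures is part of the primary outcome, and the Discussion says the study is meant to supply effect sizes for planning the full-scale trial. A masking procedure that is unclear here is likely to be carried forward.

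**Working it through.** No figure in the protocol bears on this point and no arithmetic applies. The check is a comparison of the statements on who does what and who knows what.

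**Follow-up anthropometry and fitness**

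1. *Who knows the allocation?* The chief investigator does, from the moment each envelope is offered. The research team as a whole is said to be unmaskable.
2. *Who is kept apart from the assessments?* Only the person who generates the sequence. No such separation is stated for the person who offers the envelopes.
3. *Who collects data?* The chief investigator, with no exception for the measures said to be blinded.
4. *Does the timing remove the problem?* At baseline, yes: envelopes are offered only after the baseline assessments, so whoever measures then cannot yet know the group. At follow-up, no: the section on baseline and post-intervention measurements has every test repeated after the intervention.
5. *Does the text say who takes the follow-up measurements?* No. That section describes them in the passive and gives the named investigator only the confirmation of eligibility.

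Two readings remain. If collecting data means gathering and entering forms completed by someone else who is blind to group, the statements are compatible. If it means taking the measurements, the blinding statement is false. The article does not say which reading applies.

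**Blood assays**

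1. *Are they blinded?* No. They are contrasted with the blinded measures, and a reason is given for the difference.
2. *Who runs them?* A member of the research team, in-house. The article's wording about the same member could mean one operator for all assays or a person who also has other trial tasks.
3. *When?* Samples are frozen until analysis, so even baseline samples may be assayed after allocation is known.
4. *Is there an analyst step?* The article itself describes calibration curves and peak-area calculation.
5. *Is a coding system available?* Yes. Codes are already planned for names. The article does not say that tubes carry only the code, or that the assayist lacks the link to allocation.

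Lipid profile and glucose come from a finger-prick sample read by an automated analyser at the visit. Coding of stored serum does not apply to them.

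**The case against.** The strongest reply is that the masking section is coherent as it stands: a general rule that the team cannot be masked, followed by a specific exception for anthropometry and fitness assessors. The contrast drawn with the assays suggests that those assessors are people other than the assayist. A specific commitment to blinding should outweigh a general sentence in a data-handling section, and the assessor's identity is the kind of detail an article leaves to the full protocol.

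Much of this stands. A reader might infer that the article flatly contradicts itself or that the blinding claim is already shown to be false. The documents do not support that, because nowhere do they say that the chief investigator takes the follow-up measurements. The missing name of an assessor is not the point either. What remains is that the article prints both statements without saying how they fit together.

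On the assays, it is fair to reply that the choice is disclosed and reasoned, that ELISA results are less open to observer influence than a tape measure, and that analyst discretion is possible rather than demonstrated. So this part is an inexpensive improvement and does not expose an inconsistency.

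A reader might also infer that unblinded assays would spoil the oxidised LDL standard deviation wanted for the future sample size. That does not follow: a constant shift applied to one arm moves that arm's mean and leaves the within-arm standard deviation unchanged. The exposure is in the between-group contrasts and in the androgen classification.

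**Conclusion.** The point holds in a limited form. The masking and data-collection sections must be reconciled, because the claim of blinded anthropometry and fitness assessment would be false if the chief investigator takes the follow-up measurements. The decision to leave the assays unblinded rests on a claim of objectivity that the article's own description of calibration-curve and peak-area steps does not fully bear out, and the exposure can be avoided.

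The size of any bias cannot be quantified: the documents give no information on how far an unblinded assessor or analyst might shift a reading, and any figure would only restate an assumption. The primary outcomes are feasibility and acceptability, and the measures affected are secondary, so the matter is worth correcting but does not threaten the main purpose of the study. The first part rests on the plain wording of the two sections. The second assumes that the assayist, as a research team member, knows or could learn the allocation.

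**What to change.** 1. **Randomisation and masking.** State that serum aliquots carry only the pseudonymised code already planned, with a suffix that does not reveal the visit; that the analyst sees neither group nor visit; and that allocation is merged only after the assay results are locked. The cost is relabelling, plus one condition: someone other than the assayist must hold the link. The researcher who generates the sequence could do so.
2. **Data collection, monitoring, management and storage.** State that post-intervention anthropometry and the fitness test are done and recorded by an existing team member who does not know the allocation, and that the chief investigator only compiles and enters the forms. This is a division of tasks within the team and is not meant to need new staff, but the article does not give the team's size, so the sponsor must confirm that it is workable.
3. **If the second change is not possible,** delete the statement that anthropometric and fitness assessors are blinded and report those measures as unblinded. This costs nothing beyond the edit.
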